#### **10.2.4. Reporting of serious adverse events and serious adverse device effects**

When reporting adverse events, all pertinent data protection legislation must be adhered to.

The serious adverse event report should contain the following information\*:

1. Study identifier (EudraCT number if applicable)
2. Participant's unique study number
3. Date of birth
4. Event description
5. Start date of event
6. Laboratory tests used and medical interventions used to treat the SAE
7. Planned actions relating to the event, including whether the study device was discontinued
8. Statement on the patient's current state of health
9. Criterion for seriousness (i.e. death, life threatening, hospitalisation, disability/incapacity or other)
10. Evaluation of causality (including grade of relatedness) with the following (more than one may apply):
  - a. the investigational treatment/medical device
  - b. the clinical study/a study specific procedure
  - c. other: e. g. concomitant treatment, underlying disease
11. Date of procedure
12. Reporter's name, date and signature

\*In the case of incomplete information at the time of initial reporting, all appropriate information should be provided as soon as this becomes available.

The relationship of the SAE to the investigational treatment / medical device should be assessed by the investigator at site, as should the anticipated or unanticipated nature of any SAEs and SADEs.

##### **10.2.4.1. UK**

All SAEs whether or not deemed investigational method/device related and whether anticipated or unanticipated must be reported to the Sponsor by email or fax within 24 hours (one working day) of the Investigator learning of its occurrence.

SAEs should be reported to:

[name]

Cambridge University Hospitals

NHS Foundation Trust  
[name]  
[name], UK  
[contact]  
[contact]  
E-mail: [[contact]](mailto:[contact])

A written report must follow within five working days and is to include a full description of the event and sequelae, in the format detailed on the Serious Adverse Event reporting form. If applicable, the Sponsor will notify the competent authority of all Serious Adverse Events in line with pertinent legal requirements.

The Investigator will notify the Research Ethics Committee (REC) in UK of all Serious Adverse Events in line with pertinent legal requirements. The Investigator will inform the Sponsor about all reports sent to the reporting organisation including follow-up information and answers by the reporting organisation. The local principal investigator is responsible for informing other site principal investigators and the CI of all SAEs.

The regulatory authority (MHRA) will be notified of all SAEs as soon as possible within ten days of the event occurring during the study. The REC will be notified of all unexpected and related SAEs within 15 days of the occurrence of the event.

#### **10.2.4.2. Switzerland**

All SAEs, device deficiencies and health hazards that require measures are reported to the Principal Investigator by the study team within 24 hours after becoming aware of the event. Device deficiencies are assessed regarding their potential to lead to an SAE. SADE and device deficiencies with SADE potential will be reported to the Coordinating Investigator by the study team within 3 days. SAEs will be evaluated by the Sponsor and Principal Investigator with regard to causality and seriousness.

They should be reported to:

[name]  
Department of Diabetes, Endocrinology, Clinical Nutrition and Metabolism  
Inselspital, Bern University Hospital  
University of Bern, Bern  
Switzerland

[contact]

Email: [[contact]](mailto:[contact])

The Sponsor and Principal Investigator reports to the Ethics Committee promptly any serious adverse event which has a causal relation with the medical device, comparator or procedure/test method or where a causal relation appears to be possible (Art. 33 ClinO-MD).

In order to ensure prompt notification, the Sponsor and Principal Investigator can initially submit an incomplete notification.

If safety and health hazards that require measures must be taken immediately during the conduct of the investigation, the Sponsor and Principal Investigator notifies the Ethics Committee within 2 days of these measures and the circumstances which made them necessary (Art. 34 ClinO-MD). SADE and device deficiencies with SADE potential will be reported to the Sponsor-Investigator by the study team within 7 days.

All SADEs, DD with SADE potential and safety measures will also be notified via the local materiovigilance system to Swissmedic.

Pregnancies will be reported within a maximum of 24 hours to the Sponsor-Investigator and result in withdrawal of the study subject without any follow-up procedures due to lack of safety-concerns in the event of pregnancy occurrence.

An Annual Safety Report (ASR) is submitted by the Sponsor and Principal Investigator to the Ethics Committee, yearly (Art. 35 ClinO-MD). The ASR contains a list of all SADEs and DDs and a report on their degree of seriousness, causal relationship with the MD and procedure and on subjects' safety.

An End of study notification will be sent 15 days after the end of study to the Ethics Committee and a final report will be sent to the Ethics Committee 1 year after study completion. Other reporting will be done according to provisions of MD vigilance as per Art. 87-90 MDR (Art. 33 para 4.b ClinO-MD) and Art. 67 MedDO.

Any interruption will be communicated within 15 days to the Ethics Committee after interruption (if interruption is safety-related: within 24hrs).

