| End of study assessments                              | Weight, waist hip ratio and blood pressure will be measured and a blood sample will be taken for measurement of HbA1c, fasted lipid profile, renal and liver function. Urinary ACR will be measured. Human factors questionnaires will be completed and a subset of participants will participate in an interview study. Study devices will be returned and participants will resume their usual insulin therapy and standard glucose monitoring.                                                                                    |
| Procedures for safety monitoring during trial         | 
Standard operating procedures for monitoring and reporting of all adverse events and adverse device events will be in place, including serious adverse events (SAE), serious adverse device effects (SADE) and specific adverse events (AE) such as severe hypoglycaemia.
 
A data safety and monitoring board (DSMB) will be informed of all serious adverse events and any unanticipated serious adverse device effects that occur during the study and will review compiled adverse event data at periodic intervals.
 |
| Criteria for withdrawal of patients on safety grounds | 
A participant may terminate participation in the study at any time without necessarily giving a reason and without any personal disadvantage. An investigator can stop the participation of a participant after consideration of the benefit/risk ratio. Possible reasons are:
 
 
1. Participant is unable to demonstrate safe use of study devices as judged by the investigator
 
                                                                                              |

2. Serious adverse events
3. Significant protocol violation or non-compliance
4. Decision by the investigator, or the Sponsor, that termination is in the participant's best medical interest
5. Pregnancy, planned pregnancy, or breast feeding
6. Allergic reaction to insulin or severe allergic reaction to adhesive surface of infusion set or glucose sensor
7. Technical grounds (e.g. participant relocates)

Efforts will be made to retain participants in follow up for the final primary outcome assessment even if the intervention is discontinued, unless the investigator believes that it will be harmful for the participant to continue in the trial.

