#### **6.1.2. Exclusion criteria for all countries**

1. Type 1 diabetes
2. Current use of insulin pump
3. Current use of any closed-loop system
4. Any physical/psychological disease or medication(s) likely to interfere with the conduct of the study and interpretation of the study results, as judged by study clinician
5. Known or suspected allergy against insulin
6. Pregnancy, planned pregnancy, or breast feeding
7. Severe visual impairment
8. Severe hearing impairment
9. Medically documented allergy towards the adhesive (glue) of plasters
10. Serious skin diseases located at places of the body, which potentially are possible to be used for localisation of the glucose sensor
11. Illicit drugs abuse
12. Prescription drugs abuse
13. Alcohol abuse

Potential participants with diabetes related retinal disease will not be excluded from the trial. An individualised risk approach will be used, and we will consider delaying recruiting people undergoing active treatment of proliferative retinopathy / maculopathy until treatment is complete.

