## **8.8. Participant withdrawal criteria**

The following pre-randomisation withdrawal criterion will apply:

1. Participant is unable to demonstrate safe application of insulin therapy as judged by the investigator.

The following pre- and post-randomisation withdrawal criteria will apply:

2. Participant is unable to demonstrate safe use of insulin injections or study insulin pump, CGM and/or closed-loop during post randomisation training period as judged by the investigator.
3. Participants may terminate participation in the study at any time without necessarily giving a reason and without any personal disadvantage
4. Significant protocol violation or non-compliance
5. Recurrent severe hypoglycaemia events related to the use of the closed-loop system
6. Recurrent severe persistent hyperglycaemia events/DKA unrelated to infusion site failure and related to use of the closed-loop system
7. Decision by the investigator or the Sponsor that termination is in the participant's best medical interest
8. Allergic reaction to insulin, or severe reaction to adhesive surface of infusion set or glucose sensor

Participants who are withdrawn for reasons stated in (2) to (8) will be invited to provide a blood sample and complete questionnaires at the end of the planned study intervention.

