#### **10.1.4. Serious Adverse Event**

A serious adverse event (SAE, ISO 14155, 3.45) is an adverse event that:

- led to a death
- led to a serious deterioration in the health of the participant, users, or other persons that either resulted in:
  - a life threatening illness or injury
  - a permanent impairment of a body structure or function including chronic diseases
  - in-patient hospitalisation or prolonged hospitalisation
  - medical or surgical intervention to prevent life-threatening illness or injury or permanent impairment to a body structure or a body function
- led to foetal distress, foetal death or a congenital abnormality or birth defect including physical or mental impairment

A planned hospitalisation for pre-existing condition, or a procedure required by the study protocol, without a serious deterioration in health, is not considered to be a serious adverse event.

More than one of the above criteria can be applicable to one event. Life-threatening in the definition of a serious adverse event or serious adverse reaction refers to an event in which the participant was at risk of death at the time of the event; it does not refer to an event which hypothetically might have caused death if it were more severe. Medical judgement should be exercised in deciding whether an adverse event or reaction is serious in other situations.

Important adverse events or reactions that are not immediately life-threatening or do not result in death or hospitalisation but may jeopardise the participant or may require intervention to prevent one of the other outcomes listed in the definition above, should also be considered serious.

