#### **10.2.6. Reporting of pregnancy**

Study participants will not routinely be tested for pregnancy as part of the trial follow up process. Any pregnancy which does occur during the course of the study should be reported to the Sponsor as indicated in section 10.2.4 immediately. In the UK it is at the investigator's discretion to decide whether the individual should be instructed to stop study treatment.

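### Swiss and German text ends all follow-up when a participant becomes pregnant, which conflicts with the trial-wide retention and safety follow-up provisions; section 8.8 does not name pregnancy

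*Protocol*

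**What the plan says.** **At entry.** Section 6.1.2 excludes "Pregnancy, planned pregnancy, or breast feeding" in all countries.

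**After entry, trial-wide.** The synopsis lists pregnancy as item 5 of the possible reasons for stopping, under a permissive lead-in: "An investigator can stop the participation of a participant after consideration of the benefit/risk ratio". Directly after that list it says: "Efforts will be made to retain participants in follow up for the final primary outcome assessment even if the intervention is discontinued", except where the investigator believes that continuing would harm the participant. Section 8.8 has its own list of eight withdrawal criteria, and pregnancy is not named in it. It continues: "Participants who are withdrawn for reasons stated in (2) to (8) will be invited to provide a blood sample and complete questionnaires". This offer is timed for when the scheduled intervention would have finished.

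**After entry, by country.** Sections 10.2.4.2 and 10.2.4.4 use the same words: a pregnancy is to be reported within 24 hours and will "result in withdrawal of the study subject without any follow-up procedures due to lack of safety-concerns in the event of pregnancy occurrence". Section 10.2.6 has a UK rule: "In the UK it is at the investigator's discretion to decide whether the individual should be instructed to stop study treatment".

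**Safety follow-up, trial-wide.** Section 10.1.4 counts as serious any adverse event that "led to foetal distress, foetal death or a congenital abnormality or birth defect including physical or mental impairment". Section 10.2.1 keeps reporting open until two weeks after participation ends and follows events that are still continuing at discontinuation. Section 9.2 includes participants who withdraw in the safety evaluation over 26 weeks, and section 13.3 tabulates safety data for drop-outs and withdrawals.

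**The concern.** A Swiss or German site with a pregnant participant finds two instructions. Its own country section says to withdraw her and do nothing further. The general sections say to try to keep her for the final HbA1c, to count her in the 26-week safety evaluation, and to follow any continuing adverse event. A site will usually act on the section written for its country, so the general provisions would be set aside there.

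Two things would be lost. The first is safety information: a foetal event that 10.1.4 treats as serious could arise inside the reporting window and go unrecorded because nobody is asked to look. The second is the 26-week HbA1c of a randomised participant, which would be missing because of a rule and not because she declined.

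The gap in section 8.8 adds to this. The end-of-period sample is offered by reference to numbered criteria, and pregnancy is not among those named. A site in any country has to decide for itself whether the offer applies.

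**Working it through.** **1. The no-follow-up clause against each general provision.**

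- *Synopsis retention sentence.* It comes straight after the list that names pregnancy and applies when the intervention has been discontinued. Its only exception is expected harm. The Swiss and German text gives an absence of safety concerns as its reason, which does not meet that exception. Conflict.
- *Section 10.2.1.* An adverse event still open when the participant leaves is to be followed to its outcome or until no further change is expected. That is a follow-up procedure after withdrawal. Conflict. Section 10.2.1 also equates the end of participation with completion of the final visit. A participant withdrawn with no further procedures has no such visit, so the end of her reporting window is unclear.
- *Section 10.1.4.* The foetal criteria can be applied only if someone asks about the pregnancy. Within the window, the clause removes the occasion to ask. Conflict in effect.
- *Sections 9.2 and 13.3.* Including withdrawn participants could be met formally with data up to withdrawal. But 9.2 sets the evaluation over 26 weeks, and the clause prevents that span from being covered. Conflict, though less direct than the first two.

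**2. Where the clause applies.** One Swiss site (Bern) and two German sites (Freiburg, Bad Mergentheim).

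**3. Synopsis list against section 8.8.** Pregnancy is named in the first and not in the second. The 8.8 offer covers criteria (2) to (8). A pregnancy could enter through criterion 3 (the participant's own choice) or criterion 7 (investigator or sponsor judges stopping to be in her best interest). Both are interpretations.

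**4. Size of the effect on the primary analysis.** Inputs from section 13.11: difference 0.8% HbA1c, SD 1.2, two-sided α 0.05, power 90%, 96 participants, raised to 224, dropout 20%.

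The plan's figure: n per group = 2(z₀.₉₇₅ + z₀.₉₀)² × SD² / difference² = 2 × (1.960 + 1.282)² × 1.44 / 0.64 ≈ 47.3, rounded up to 48 per group, 96 in total. This reproduces. Power at 48 per group is 90.4% by the normal approximation and 89.8% by the t test.

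With 20% dropout, 224 × 0.8 ≈ 179 participants are evaluable. The protocol gives no pregnancy rate, so the number of final HbA1c values lost to pregnancy is an assumption, taken from 0 to 5. With m = (179 − lost)/2 per group, power = Φ(difference / (SD × √(2/m)) − 1.96):

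| Values lost | Share of 224 | Power at 0.8% | Power at 0.5% |
|---|---|---|---|
| 0 | 0% | 99.38% | 79.6% |
| 1 | 0.4% | 99.36% | 79.4% |
| 2 | 0.9% | 99.33% | 79.2% |
| 5 | 2.2% | 99.26% | 78.5% |

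The 0.5% column uses the difference that section 13.11 calls clinically meaningful. Five lost values cost about 0.1 percentage point of power at 0.8% and about 1 point at 0.5%.

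**The case against.** The case for leaving the text alone has several parts, and most of them limit the point without removing it.

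- *Late birth outcomes.* A reader might infer that the clause causes congenital abnormalities and foetal deaths to be missed at the Swiss and German sites and caught elsewhere. The protocol does not support that. Section 10.2.1 admits no new adverse events after the reporting period in any country, so an outcome that first appears months later is outside collection everywhere. The clause can affect only the reporting window and events already open.
- *Country differences.* A reader might infer that the UK and the Swiss and German rules contradict each other. They are labelled national rules. The UK sentence concerns stopping study treatment and not leaving the study, and it agrees with the permissive synopsis. This is different handling within one trial, not a contradiction.
- *Intention to treat.* A reader might infer that these participants drop out of the analysis. They do not. Section 13 includes all randomised participants, 13.1 includes data from withdrawals as appropriate, section 15 keeps data obtained before withdrawal, and HbA1c is also measured at three months. At most the 26-week value is missing.
- *Section 8.8.* Criteria 3 or 7 can cover a pregnancy, so it is not shut out of the end-of-period sample. That is fair, but it rests on interpretation, and the clause would still bar the sample in Switzerland and Germany.
- *Strength of the promise.* The synopsis offers efforts and 8.8 an invitation; neither guarantees collection. This also stands, but a rule that forbids follow-up is incompatible even with an effort.
- *Rarity.* Switzerland and Germany both exclude women of childbearing potential without safe contraception (6.1.3, 6.1.5), so cases there should be rarer still. This bears on size and not on whether the texts agree.

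What remains is the conflict between the two country clauses and the general retention and safety provisions, and the omission of pregnancy from 8.8.

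**Conclusion.** The conflict is real and narrow. As written, sections 10.2.4.2 and 10.2.4.4 stop the collection of safety and end-of-period data that the protocol elsewhere sets out to collect, and section 8.8 leaves it unclear whether its offer reaches someone who stops because of pregnancy.

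The effect on the HbA1c result and on power is negligible. This rests on an assumed 0 to 2 pregnancies among 224 participants, fewer of them in Switzerland and Germany, and it holds even at five. The consequence is possible under-recording of safety events within the reporting window and a missing 26-week value for any participant concerned at the Swiss and German sites. It is worth correcting because rare events are easily lost when a site is told that nothing further is needed, and because the correction is cheap. No view is taken on which clinical rule for pregnancy is right.

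**What to change.** Reconcile the synopsis withdrawal text and sections 8.8, 10.2.4.2, 10.2.4.4 and 10.2.6 so that:

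1. the no-follow-up wording in the Swiss and German sections no longer conflicts with the synopsis retention sentence, the safety evaluation of withdrawn participants (9.2, 13.3), or the follow-up of adverse events within the terms of 10.2.1;
2. the 8.8 invitation clearly covers anyone who stops because of pregnancy. This can be done by extending the invitation, without making pregnancy a withdrawal criterion;
3. collection of follow-up data does not depend on whether study treatment continues.

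Whether pregnancy leads to withdrawal or to stopping study treatment is for the sponsor to settle, and national differences may stay as labelled. If the sponsor wants outcomes beyond the reporting window, that needs its own provision; a reference to 10.2.1 would not supply it.

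The cost is wording in five places. The serious adverse event form and the end-of-period sample already exist.

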#### **10.2.4.3. France**

All serious adverse events will be managed and reported in compliance with all applicable regulations and included in the final clinical study report.

#### **10.2.4.4. Germany**

The reporting of serious adverse events (SAEs) and product defects (DDs) must be carried out in accordance with the European Regulation 2017/745 (MDR) in conjunction with the Medical Device Law Implementation Act (MPDG) and must be applied for or reported to the higher federal authority.

Any reportable event as defined in Article 80 MDR or Section 64(1) MPDG that indicates an immediate risk, death, serious injury, or serious illness and that requires immediate corrective action for other patients/proband, users, or other persons, or that involves new knowledge should be reported promptly, but no later than 2 calendar days after the Sponsor becomes aware of a new reportable event or new information related to a previously reported event.

All other reportable events described in Article 80 MDR or Section 64 Section 1 MPDG, or a new finding/update thereto should be reported immediately, but no later than 7 calendar days after the date the sponsor becomes aware of the new reportable event or new information related to a previously reported event.

All SAEs, device deficiencies and health hazards that require measures must be reported by the study investigators to the Sponsor within 24 hours after the SAE becomes known using the "Serious Adverse Event" form.

Device deficiencies are assessed regarding their potential to lead to an SAE. SAEs will be evaluated by the Sponsor and Principal Investigator with regard to causality and seriousness.

Pregnancies will be reported within a maximum of 24 hours to the Sponsor-Investigator and result in withdrawal of the study subject without any follow-up procedures due to lack of safety-concerns in the event of pregnancy occurrence.

SAEs should be reported to:

University Hospital Freiburg

Klinik für Innere Medizin II – Studienbüro

[name]

[name],

Germany

[contact] [contact]

E-mail: [[contact]](mailto:[contact])

